#### Transthoracic echocardiography

All participants will undergo transthoracic echocardiography performed by British Society of Echocardiography accredited physiologists at baseline and week 12 visits.^34^ Assessment of tissue Doppler indices of diastolic filling and speckle tracking for global longitudinal strain, LV size and systolic function and valve function will be undertaken.^34^

#### MRI

Unless contraindicated, all participants will be invited to undergo cardiac MRI (CMR) with assessment of body composition and organs (including liver, kidneys and pancreas), as outlined in figure 2. Participants who are unable to tolerate the full protocol will be offered a shortened ‘core dataset’ CMR protocol, discussed later in the text. MRI will be performed using either a 1.5 or 3-Tesla platform with an 18-channel phased-array cardiac receiver coil.^35^ Baseline and follow-up scans will be completed at the same field strength.

**Figure 2 F2:**
[figure not shown]
Cardiac Magnetic Resonance (CMR) imaging protocol. CMR imaging will be undertaken at 1.5 or 3-Tesla with optional 31-phosphorus spectroscopy at centres where available. Baseline and week 12 CMR will be performed at the same field strengths. 2C/3C/4C: two chambers, three chambers, four chambers.LA: left atrium, LGE: late gadolinium enhancement; LMS: liver multi scan; LV: left ventricle

#### MRI assessment of body composition

Each participant’s body composition, liver, pancreas and kidneys will be assessed using a multiparametric imaging tool COVERSCAN (PERSPECTUM, Oxford, UK) which will be conducted before the cardiac sequences are acquired. The COVERSCAN has been validated in large prospective studies of multiorgan effects of COVID-19 with methodology previously published.^36^,^39^ To assess body composition, a stack of 3–4 axial 3D T-1 weighted multiecho gradient echo Dixon VIBE sequence will be acquired extending from the top of ninth thoracic vertebrae (T9) to the tip of the femoral condyle.

Liver and pancreas multiparametric assessment will be conducted using the LiverMultiScan (LMS) acquisition protocol (PERSPECTUM, Oxford, UK)^40^ with assessment of liver adiposity (with proton density fat fraction (PDFF)), liver iron content (using T2*) and inflammation (with T1 Modified Look-Locker Inversion recovery pulse sequence (MOLLI)).^40^ For the assessment of pancreas, a PDFF map and an MOLLI T1 map will be acquired showing the head body and tail of pancreas in a single slice.

A single coronal T1 map of both kidneys will also be acquired.

#### Cardiac Magnetic Resonance assessment of myocardial structure, function and perfusion

Following localisers, balanced steady-state free precession (bSSFP) LV cine images will be acquired in two-chamber, three-chamber and four-chamber views. Myocardial tissue will be characterised with a single T1 map (MOLLI) acquired at the junction of the basal/mid LV short-axis level and a single T2 map at junction of the basal/mid LV short-axis level acquired pre-contrast. Unless contraindicated, participants will undergo stress and rest perfusion with pharmacological vasodilator adenosine (140 µg/kg/min for 2–3 min). If a satisfactory haemodynamic response is not achieved (a drop in systolic BP of 10 mm Hg and/or a rise in heart rate of 10 bpm) after 2 min, the dose will be increased to a maximum of 210 µg/kg/min. During peak stress, a gadolinium-based contrast agent (gadoterate meglumine or gadobutrol, depending on availability at each recruitment site) will be injected (at 0.05 mmol/kg) at 5 mL/s, followed by a 20 mL bolus of normal saline. Data will be acquired using a multislice, free breathing saturation recovery pulse sequence with fast low-angle short readout acquired over 60 heart beats, in three short-axis slices as previously described.^41^ Myocardial blood flow (MBF) will be quantified using a dual pulse sequence acquisition with fully automatic inline calculations as previously described.^8 42^ Rest images will be performed approximately 10 min after stress with a further 0.05 mmol/kg bolus of contrast. In the meantime, short-axis stack images will be acquired using cine imaging (bSSFP) covering the entire LV. Late gadolinium-enhanced images (inversion recovery gradient echo sequence) and postcontrast T1 maps (MOLLI) will determine focal and diffuse myocardial scar, respectively. Aortic cine images will be acquired in the ascending and descending aorta at the level of the pulmonary artery bifurcation. Pulse pressure will be measured simultaneously to allow calculation of aortic distensibility which has been postulated to be the key determinant of LV remodelling in T2D.^43^

#### The ‘core data set’ CMR protocol

Core dataset CMR protocol will be employed at the supervising clinician’s discretion for patients unable to lie flat for the duration of the full protocol. To assess body composition, a stack of 3–4 axial 3D T-1 weighted multiecho gradient echo Dixon VIBE sequence will be acquired extending from the top of ninth thoracic vertebrae (T9) to the tip of the femoral condyle. This will be followed by localisers, a set of two-chamber, three-chamber and four-chamber cines, precontrast mid-level T1 map, an adenosine stress perfusion protocol, short-axis LV stack, postcontrast mid-level T1 map and a segmented LGE imaging, using the protocol as discussed above.

### Image analysis

The images will be anonymised and labelled with a unique study ID. Analysis of body composition, liver, pancreas and kidney imaging, as well as volumetric analysis of the left and right ventricular and atrial data, will be undertaken by PERSPECTUM.^40^ The quantitative assessment of myocardial perfusion, myocardial strain and strain rates will be performed by the trained core lab staff at Leicester blinded to all participant details and allocation groups.

#### Analysis of cardiac sequences

Cardiac volumes and mass, left and right ventricular stroke volume and ejection fraction will be calculated by PERSPECTUM.^37^ Experienced CMR analysts blinded to treatment allocation will use CVi42 (Cardiovascular Imaging, Canada) to manually trace the endocardial borders in the end-diastolic and end-systolic phases in each of the short-axis views, following the standard UK Biobank evaluation approach.^44^ This analysis will produce, for both the left and the right ventricle the end diastolic volume, end systolic volume, stroke volume and ejection fraction. Additionally, LV muscle mass and wall thickness will be determined from the function data.

Analysis of LV strain, quantitative analysis of perfusion data, calculation of the extracellular volume (ECV) will be performed by an experienced operator in Leicester using CVI42 software. Assessment of peak diastolic filling rate, systolic global longitudinal and circumferential strain, global longitudinal strain and circumferential and longitudinal peak early diastolic strain rates will be performed as previously described.^35^ Epicardial adipose tissue volume will be quantified in cubic centimetres.

Late gadolinium enhancement will be qualitatively assessed in all 16 segments of the American Heart Association model by an expert CMR cardiologist as per the Society for Cardiac Magnetic Resonance guidance.^45^ For ECV calculation, a single region of interest will be manually drawn in the LV septum of the short axis on the native and postcontrast T1 maps, as previously described.^46^ Segments containing myocardial infarction or non-ischaemic enhancement (as judged by an experienced CMR expert) will be excluded.^47^ ECV value will be calculated using the previously described formula.^46^

Quantitative analysis of perfusion data will be performed as previously described using an automated AI tool.^41^ The myocardial perfusion maps will be visually inspected for quality and discarded if errors are found. The MBF values for each of the 16 myocardial segments will be recorded for stress and rest, and global values will be automatically calculated as averages. Rate pressure product (RPP) will be calculated (heart rate×systolic BP) and rest MBF will be corrected for RPP as per best practice.^48^ Myocardial perfusion reserve (MPR) will then be automatically calculated for each segment as stress MBF/rest MBF and results recorded.^41^

Ascending, descending and mean aortic distensibility will be measured using Java Image Manipulation (Xinapse Software, Essex, UK), as previously described.^43^

#### Body composition and analysis of body composition and extracardiac organ images

For delineation of subcutaneous adipose tissue (SAT), visceral adipose tissue (VAT) and Skeletal Muscle Index (SMI), a single two-dimensional section positioned at the third lumbar (L3) vertebrae will be extracted from whole-body Dixon MRI. The L3 section will be selected as it has been shown to be the most representative of the body skeletal muscle distribution and it is accurate in the assessment of the total subcutaneous and visceral fat volumes.^49^,^51^ The cross-sectional areas of SAT, VAT and skeletal muscle will be manually segmented in the ITK-SNAP software (V.3.8.0) tool^50^ and the resulting values will be reported as centimetres squared. The SMI will be calculated by indexing the centimetres squared values of lean muscle to the squared height of the participant (centimetres squared/metres squared).^40^

Liver MRI scans will be analysed using PERSPECTUM’s LMS technology.^36^ This software automatically delineates the liver from cT1, T2* and PDFF image maps, excluding major vessels within the image section as previously described.^36^ For each liver, a metric of PDFF, T2* and cT1 (cT1 is a measurement of T1 that has been corrected for the confounding effects of iron and standardised to 3-Tesla) will be yielded as previously described.^36^ Pancreas images will be analysed by manually placing, on PDFF maps when possible, a single region of interest of 10 mm within the head, body, and tail of the pancreas, avoiding blood vessels and ducts. The output T1 will be standardised to 3 Tesla for both the liver and pancreas. Kidney T1 maps will be analysed by manually placing on T1 maps up to 10 regions of interest around the renal cortex.

### Optional assessments and substudies

#### Optional 24-week visit

Participants will be invited for an optional visit at 24 weeks, to assess the delayed remodelling with a focused non-contrast CMR scan to assess LV volumes, mass and aortic distensibility, a 6MWT and KCCQ score.

#### Optional qualitative substudy evaluation

Both MRP and control group participants will be invited for an optional focused semi-structured one-on-one interview after their 12-week visit to identify barriers and enablers to MRP, share their views on healthy eating and health, and their experiences. This includes those who complete the programme or drop out. Including participants from the control group will enable comparison of MRP experiences against health coaching, highlighting challenges in self-directed lifestyle changes. The interview topic schedule was created with input from a health psychologist and local patient and public involvement (PPI) group (available in online supplemental file: appendix 3).

#### Optional musculoskeletal substudy

At the Leicester site only, participants in the MRP and control group will be invited to take part in the musculoskeletal substudy with additional single visit for calf and quadriceps muscle strength testing, physical performance battery test,^52^ skeletal muscle biopsy^53^,^55^ and skeletal muscle ^31^P-MRS.^56^,^58^ Participation in this substudy is optional for participants.

#### ^31^Phosphorus MR spectroscopy

Where available at recruitment sites on a 3.0 Tesla MR system, participants will be offered the option of undergoing ^31^P-MRS at the beginning of the cardiac protocol, using methodology as described previously.^59^ In brief, ^31^P-MRS will be performed to assess myocardial PCr/ATP ratio from a voxel placed in the midventricular septum, with patients lying supine and a ^31^P-transmitter/receiver cardiac coil (Rapid Biomedical) placed over the heart on a 3.0 T MRI system.^59 60^

### Randomisation

Randomisation (1:1) will occur at the end of the baseline visit after data collection, using the ‘blockrand’ package in R^61^within the REDCap (Research Electronic Database Capture) system . The allocation list will be concealed from the user and non-editable once uploaded. REDCap’s randomisation module will reveal participant allocation only at the moment of randomisation, ensuring strict allocation concealment. The randomisation will be stratified by sex, ethnicity and baseline SGLT2-i use.

### Study interventions

#### Baseline optimisation of medical therapy for heart failure

All eligible participants entering the study will be offered a sodium glucose co-transporter 2 inhibitor (SGLT2-i), if not already prescribed, in line with the current National Institute for Care and Clinical Excellence guidance.^27^ There will be an approximate 4-week interval between the commencement of SGLT2-i and the start of MRP to take effect in order to observe its full metabolic and CV outcome impact.^27^ Given the evidence of benefit of SGLT2-i in HFpEF and the low risk of hypoglycaemia and hypotension is minimal,^32^ SGLT2-i will not be stopped during MRP. Individuals with underlying type 2 diabetes mellitus will be provided ketone measuring strips on initiation of MRP.

#### Meal replacement plan

Those allocated to the MRP will be referred to our commercial partner Counterweight and follow the ‘Counterweight Plus’ program with 12-week MRP.

The MRP follows ~810 kcal/day meal replacement diet with a macronutrient ratio of 40% protein, 50% carbohydrates and 10% fat. The MRP regimen includes four daily meal packs, 100 mL of semiskimmed or non-dairy milk, non-starchy vegetables such as leafy greens or cruciferous vegetables and encourages ~2 L of non-caloric fluid intake daily. The diet transitions to maintenance after achieving a 50% excess weight loss or by week 12. Those who are morbidly obese (body mass index ≥40 kg/m^2^) at baseline will undergo a stepwise gradual calorific reduction from approximately 1500 kcal/day to 810 kcal a day over 1–2 weeks, depending on baseline body weight.

Alongside the MRP, all participants receive health behaviour coaching and medication adjustments by clinicians, with biweekly clinical reviews and remote monitoring tools provided for safety which include automatic BP machine and weighing scales, and ketone strips in those with T2D. Medications will be reviewed prior to starting the diet by the study clinician(s) and will be advised to stop or reduce antihypertensives and glucose-lowering agents as deemed appropriate. The approach is outlined in online supplemental file: appendices 1 and 2 for adjustment protocols for antihypertensives and glucose-lowering medications. Glucose and BP monitoring will guide clinical reviews, conducted either in person or remotely based on participant preference.^62^ Routine reviews by Counterweight dieticians will occur remotely every 2 weeks. Based on participant and PPI feedback, the number of contacts with the research team has been minimised to baseline and follow-up visits only. However, in the event of participant’s request for a review or medical issues arising during the study, a review with the study clinician(s) will be arranged. MRP participants will use digital weighing scales and BP monitors for home monitoring. The use of liquid fibre (ispaghula husk) will be recommended to all participants on MRP to reduce risk of constipation. Individuals with coexisting T2D will be provided with ketone measuring strips and advised on sick day rules with respect to their continuation of SGLT2-i therapy while on MRP. Individuals with existing gallstones will be offered a prescription of ursodeoxycholic acid to reduce the risk of flare-ups.

The ‘Counterweight Plus’ program, provided by Counterweight includes dedicated personal support from a dedicated Counterweight registered research dietitian and will have regular 1:1 appointments throughout the programme and up to 12 months post-trial. The diet programme is delivered via a digital application (‘App’) that is downloaded onto a smart phone or tablet. The Counterweight App functions include logging measurements, for example, weight, mood, reviewing progress, nutrition/physical activity educational content and goal setting. Individuals will be allocated a named ‘Counterweight dietitian/coach’ for personal support, for regular appointments and to moderated online ‘chat’ facility to enable peer support between participants, as recommended by our patient and PPI group feedback. Counterweight dietitians have undertaken formal competency-based training from Counterweight specialist dietitians, then ongoing supervision and mentoring, to maintain programme fidelity.

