### Study visits

The study will comprise two main assessment visits, at baseline and 12 weeks, with an optional third visit at week 24. An outline of study visits and measures taken during each visit is shown in table 1. Participants will have the option to split the baseline and 12-week visits into two visits in close succession if undergoing the assessments in 1 day is too onerous. Participants will be offered reimbursement for travel. Lunch will be provided during each assessment visit.

**Table 1 T1:** Overview of assessments during study visits

	Baseline visit	Week 12 visit	Week 24 visit (optional)
Visit window		±3 days	±2 weeks
Eligibility assessment	✓		
Consent	✓		
Medical history and examination	✓		
Medication review and adjustment	✓	✓	
Demographics and height measurement	✓		
Body weight recording	✓	✓	✓
Blood pressure and heart rate	✓	✓	✓
Blood sampling	✓	✓	
ECG	✓	✓	
Echocardiography	✓	✓	
CMR	✓	✓	✓
Accelerometery	✓	✓	
Health coaching (in both arms at baseline then control arm only)	✓	✓	
6MWT	✓	✓	✓
Handgrip strength	✓	✓	
Questionnaires	✓	✓	✓

6MWTSix-Minute Walk Test

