### Control group

The control group will receive standard care and dietary/exercise advice which will follow the National Health Service (NHS), National Institute for Health and Care Excellence and the European Society of Cardiology guidelines^18 26 63^ for promoting low-moderate intensity physical activity. BP and lipid management will adhere to clinical guidelines, with statin therapy adjusted based on CV risk.^63^ Health coaching advice will be provided to participants at baseline and follow-up visits.

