### Trial oversight and governance

The study sponsor is University of Leicester. A Data Monitoring Committee was not deemed necessary for this open-label RCT given the intervention is already recommended in primary care and commercially available for independent purchase. Instead, oversight will be maintained through the TSC, which will review safety data and monitor trial conduct, and have the authority to recommend trial modification or termination based on predefined stopping criteria. All safety data will be systematically collected throughout the trial using standardised case report forms, and all AEs, including serious AEs, will be reported promptly to the TSC and relevant regulatory bodies in accordance to the sponsors standard operating procedures (SOPs). Study audit will be conducted by the sponsor.

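### Contact between baseline and week 12 is much closer in the MRP arm than in control, so raw counts of non-serious adverse events by arm may not be comparable

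*Protocol article*

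**What the plan says.** **MRP arm.** The section on the meal replacement plan states: "Routine reviews by Counterweight dieticians will occur remotely every 2 weeks". It describes coaching and medication adjustment "with biweekly clinical reviews and remote monitoring tools provided for safety which include automatic BP machine and weighing scales, and ketone strips in those with" type 2 diabetes, and adds: "MRP participants will use digital weighing scales and BP monitors for home monitoring". The programme also includes a named coach and an app for logging measurements.

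**Control arm.** The only contact described is in the Control group section: "Health coaching advice will be provided to participants at baseline and follow-up visits". Under Study visits, "The study will comprise two main assessment visits, at baseline and 12 weeks, with an optional third visit at week 24", and Table 1 lists no visit between baseline and week 12.

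**Research-team contact.** The MRP section says that "the number of contacts with the research team has been minimised to baseline and follow-up visits only". It then allows for unscheduled contact: "in the event of participant’s request for a review or medical issues arising during the study, a review with the study clinician(s) will be arranged".

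**Safety data.** Trial oversight and governance says: "All safety data will be systematically collected throughout the trial using standardised case report forms". All adverse events go to the TSC, which replaces a data monitoring committee and may recommend changing or ending the trial against criteria set in advance.

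**Common to both arms.** At week 12 there is a health review, with blood pressure, blood sampling and ECG (12-week data collection visit; Table 1). Clinical records are reviewed at 12 months, giving deaths and hospitalisations (Aims; 12-week data collection visit). No distinction by arm is made for either.

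**The concern.** A standard form makes recording uniform. It does not make the opportunity to notice an event uniform. A low home blood-pressure reading, a spell of dizziness or a few days of constipation in week 3 can come to light within about two weeks on MRP. In a control participant the same event surfaces only if the participant raises it or remembers it at week 12. The trial is open-label, so participants and staff know who is being watched more closely.

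Two readings of the data could be affected. The TSC will see adverse-event counts during the trial and may act on them. The published tolerability of MRP also matters, because the Background argues for a dietary alternative partly from the 13% to 18% of semaglutide users with adverse events. If non-serious events are more frequent on MRP, a true excess could not be separated from closer observation.

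**Working it through.** The article states no adverse-event rate and no between-arm harm test, so there is no figure of its own to reproduce. Step 1 uses the article. Steps 2 to 4 are illustrations on assumed inputs.

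**1. Scheduled contacts, baseline to week 12.** On MRP, one dietitian review every 2 weeks gives 12 / 2 = 6: five before week 12 and one at about week 12. Controls have none before week 12 and one visit at week 12. I leave the clinical reviews out of the count because the article is unclear on who receives them and from whom.

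**2. Recall at a single week-12 contact (assumed: events spread evenly, all-or-nothing recall of r weeks).** The share of events older than the recall period is (12 − r) / 12:

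- r = 2: 10/12 = 83%
- r = 4: 8/12 = 67%
- r = 6: 6/12 = 50%
- r = 8: 4/12 = 33%

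**3. Effect on an apparent comparison when the true risk is equal.** The apparent risk ratio is capture on MRP divided by capture in control, whatever the true risk. With 95% capture on MRP (assumed):

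- control capture 50%: 0.95 / 0.50 = 1.90
- control capture 70%: 0.95 / 0.70 = 1.36
- control capture 90%: 0.95 / 0.90 = 1.06

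For true risks of 10% to 40%, the apparent risk differences run from 0.10 × 0.05 = 0.5 points to 0.40 × 0.45 = 18 points.

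The chance that a two-sided Fisher test at 0.05 calls the arms different can be enumerated exactly for 110 / 2 = 55 per arm and a true risk of 30% in both (assumed; the article plans no such test):

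| Capture MRP / control | Observed MRP / control | Chance of p<0.05 |
|---|---|---|
| 100% / 100% | 30% / 30% | 3.1% |
| 100% / 90% | 30% / 27% | 4.1% |
| 100% / 70% | 30% / 21% | 13.8% |
| 100% / 50% | 30% / 15% | 38.4% |
| 85% / 70% | 25.5% / 21% | 5.5% |
| 70% / 50% | 21% / 15% | 8.0% |
| 70% / 70% | 21% / 21% | 2.8% |

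The large values need full capture on MRP. With imperfect capture in both arms the effect is modest.

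**4. Drop-out pulls the other way.** The sample size section assumes up to 30% drop-out on MRP and under 10% in control. As an extreme, suppose every event in a drop-out is lost, so at most 70% of MRP events and about 90% of control events remain. With equal capture among completers the apparent ratio is 0.70 / 0.90 = 0.78, below 1. With control capture of 70% among completers it is 0.70 / (0.90 × 0.70) = 1.11, and with 50% it is 0.70 / (0.90 × 0.50) = 1.56. The direction therefore depends on quantities that the article does not give.

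**The case against.** The strongest reply is that nothing in the article says adverse events are gathered through the dietitian reviews or home devices. Monitoring is described as guiding care, the dietitians belong to a commercial partner, data are entered by the study team, and scheduled research-team contact is said to be limited to baseline and follow-up visits. Safety data are described as collected systematically, on standard forms, without distinction by arm. The enquiry schedule would normally sit in the full protocol, case report form or operating procedures, so its absence here is no fault. Closer monitoring is also part of the intervention under test.

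Much of this stands. A reader might infer that the extra contacts are the route of adverse-event collection; the article does not say so. A reader might also infer that every harm comparison is tilted, or that the 12-month record review is the only common source. Neither is supported: deaths and hospitalisations come from a record review with no arm distinction, and the week-12 health review, blood pressure, bloods and ECG are common as well. The on-request clinician review appears in the MRP section but is not clearly restricted to that arm.

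What remains does not rest on silence. The unequal contacts are stated, the devices are said to be provided for safety, and all adverse events must be reported. An event that comes to light at a two-weekly review would be expected to reach the record. On-request review is passive and does not replace scheduled enquiry.

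**Conclusion.** The point holds for non-serious, transient events only. Opportunity for detection between baseline and week 12 is unequal by arm, so raw counts of such events may not be comparable. It is a plausible detection bias, not a demonstrated one.

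It is tempting to conclude that equal true rates would necessarily show as excess harm on MRP. The documents do not support that. Capture rates are unknown, and differential drop-out could offset or reverse the effect. The ratios and test probabilities above rest wholly on assumed risks and capture shares and are not estimates for this trial. No formal harm comparison is listed among the endpoints either; the practical exposure lies in how the TSC and readers take counts by arm.

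This merits a cheap improvement, at most a should-do. Separately, the MRP section promises frequent clinical reviews to all participants and also limits research-team contact to baseline and follow-up visits. Those passages must be reconciled.

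**What to change.** - Ask every participant one identical adverse-event checklist, with the same wording and recall period, at the existing week-12 visit.
- Add a source field to the adverse-event form: week-12 checklist, dietitian or clinical review, home reading, spontaneous report, or record review.
- Base the between-arm comparison of non-serious events on the checklist, and that of serious events on the common record review over the same window from randomisation.
- Continue to report all MRP events found through the extra monitoring, labelled by source, to the TSC and in the results.
- Reconcile the statements on clinical reviews and research-team contact in the MRP section, making clear which arm each applies to.

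**Cost.** One checklist page at a visit that already takes place, one form field, and wording for the TSC report and analysis plan. No added visits, staff or devices, and no change to MRP monitoring.

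**Downside.** The comparable non-serious set rests on 12-week recall in both arms and will be less complete. Participants already past week 12 will lack the checklist; 24 had been randomised at submission, and the article does not say how many had passed that visit. Those who drop out before week 12 will also lack it, so the number without a checklist should be shown by arm.
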